## Abstract

**Background:**

Clinical trials evaluating the use of hypertonic saline in the treatment of hypovolemia and head trauma suggest no survival superiority over normal saline; however subgroup analyses suggest there may be a reduction in the inflammatory response and multiorgan failure which may lead to better survival and enhanced neurocognitive function. We describe a feasibility study of randomizing head injured patients to hypertonic saline and dextran vs. normal saline administration in the out of hospital setting.

**Methods/Design:**

This feasibility study employs a randomized, placebo-controlled design evaluating normal saline compared with a single dose of 250 ml of 7.5% hypertonic saline in 6% dextran 70 in the management of traumatic brain injuries. The primary feasibility endpoints of the trial were: 1) baseline survival rates for the treatment and control group to aid in the design of a definitive multicentre trial, 2) randomization compliance rate, 3) ease of protocol implementation in the out-of-hospital setting, and 4) adverse event rate of HSD infusion.

The secondary objectives include measuring the effect of HSD in modulating the immuno-inflammatory response to severe head injury and its effect on modulating the release of neuro-biomarkers into serum; evaluating the role of serum neuro-biomarkers in predicting patient outcome and clinical response to HSD intervention; evaluating effects of HSD on brain atrophy post-injury and neurocognitive and neuropsychological outcomes.

**Discussion:**

We anticipate three aspects of the trial will present challenges to trial success; ethical demands associated with a waiver of consent trial, challenging follow up and comprehensive accurate timely data collection of patient identifiers and clinical or laboratory values. In addition all the data collection tools had to be derived de novo as none existed in the literature.

**Trial registration number:**

NCT00878631

## Background

Hypertonic Saline provides an alternative to large volume time limited resuscitation to restore hemodynamic stability and minimize the posttraumatic organ dysfunction. There is however, no clear clinical evidence supporting the hypothesis that hypertonic saline is the optimal choice for prehospital trauma resuscitation, specifically with respect to brain injury. Most of the current evidence demonstrating anti-inflammatory and immunological properties of hypertonic saline comes from experimental models (animal and isolated cell preparations) and remains untested in humans. A recent meta-analysis demonstrated that hypotensive patients with severe head injury are twice as likely to survive if resuscitated with hypertonic saline in dextran (HSD) compared with isotonic crystalloids [1] In separate clinical trials, HSD resuscitation was associated with a reduced incidence of acute respiratory distress syndrome (ARDS), renal failure and infectious complications [2-4]. Because of the compelling current evidence suggesting the effectiveness of HSD and the known burden of traumatic brain injury (TBI) and multiorgan dysfunction, this question requires direct evaluation.

The application of rigorous clinical trial methodology in the prehospital setting requires overcoming a number of challenges unique to the setting. We conducted a feasibility study prior to implementing a larger randomized clinical efficacy trial. This feasibility study is significantly different from other prehospital trauma trials because it is designed by investigators from multiple disciplines including immunology, neurology, surgery, anaesthesia, neuropsychology and neuroimaging to address aspects of TBI not evaluated previously and employs a randomized clinical trial design and waiver of consent. In addition to the primary study objective of survival at 30 days we plan to evaluate circulating and cellular immunomodulation within the first 24 hours, neurocognitive and neuropsychological testing at 4 and 12 months, and structural damage through MRI scanning up to 4 months post trauma.

We report the methods in detail and have appended the data collection tools and case report forms for this feasibility study. All case report forms and data collection forms were created by the investigators as prior forms did not exist previously in the literature.

## Methods/Design

### Study design

The Toronto Prehospital Hypertonic Resuscitation-Head Injury and Multi Organ Dysfunction Trial (TOPHR HIT) is a randomized, placebo-controlled trial of blunt trauma patients with head injuries. The study compares a group receiving normal saline according to a paramedic's protocol, with a treatment group receiving a single dose 250 ml of 7.5% hypertonic saline in 6% dextran 70 (RescueFlow^® ^BioPhausia AB, Stockholm Sweden). The study was approved by the Canadian Therapeutic Products Directorate Control Number 092523 and registered at http://www.clinical.trials.gov. Inclusion and exclusion criteria are summarized in Additional file 1.

### Study Objective

The primary objective of this study is to report feasibility in accordance with the methodology described by Lancaster and Dodds [5], specifically addressing:

1) baseline survival rates for the treatment and control group to aid in the design of a definitive multicentre trial;

2) randomization compliance rate;

3) ease of protocol implementation in the out-of-hospital setting;

4) adverse event rate of HSD infusion.

The secondary objectives include measuring the effect of HSD in modulating the immuno-inflammatory response to severe head injury and its effect on modulating the release of neuro-biomarkers into serum; evaluating the role of serum neuro-biomarkers in predicting patient outcome and clinical response to HSD intervention; and evaluating effects of HSD on brain atrophy post-injury and neurocognitive and neuropsychological outcomes.

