### Intervention Protocol

All patients will be treated according to research medical directives (Additional File 2) based on a standardized provincial out of hospital trauma treatment protocol [6]. The study solution is started within 4 hours of the time the emergency call was received at ambulance dispatch. Samples of peripheral blood will be collected upon emergency department (ED) arrival, 12, 24 and 48 hours after ED arrival from a vein remote from the venous access site for the study infusion. Blood samples will be collected in heparinized and non-additive vacutainers by a single trained lab technician and immediately (within 1-h) shipped to a single designated laboratory for whole blood flow cytometric cellular analyses and measurement of circulating molecular immuno-inflammatory markers. Serum will be frozen for subsequent analyses. Whole blood will be incubated with saturating concentrations of the adhesion (CD62L-FITC, CD11b-PE), degranulation (CD66b-FITC, CD63-PE), apoptotic/necrotic (Annexin V-PE, 7-AAD, Active Caspase-3, CD95-Fas, CD178-FasL) markers, in conjunction with CD14-APC surface staining (to differentiate leukocyte subsets). Results will be acquired on a Becton Dickinson dual-laser (488 nm and 635 nm) BD FACSCalibur flow cytometer using CellQuest software. Serum samples will be analyzed for pro-/anti-inflammatory cytokines (TNF-α, IL-10), soluble leukocyte and endothelial-derived adhesion molecules (sICAM-1, sVCAM-1, sE-selectin, sL-selectin), pro-/anti-apoptotic molecules (sCD95, sCD95L, TNF-RI, sFas/FasL) and neuro-biomarkers of brain injury (S100B, NSE, MBP) (Additional File 3).

Magnetic Resonance Imaging on a 1.5 Tesla General Electric Signa Magnet is planned for completion at 4 months for consenting patients using a standardized protocol (Additional File 4, 5, 6, 7); a 3D 1.3 mm thick, T1-weighted, series (TE 4-2, TR 35, flip angle 35), an interleaved 3 mm thick PD and T2-weighted spin echo sequence (TE 39/80, TR 3000, flip angle 90) (Additional File 6), a gradient echo sequence and Diffusion Tensor Imaging (11 directions) (Additional File 7); tissue segmentation and parcellation including lesion quantification [7-12] using previously published in-house software as well as ANALYZE software [7,13].

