### Cellular and Molecular Biomarkers

Whole blood and circulating immuno-inflammatory markers will be measured on hospital arrival and at 12, 24 and 48 hours later

• Total leukocyte count and differential; neutrophil and monocyte surface expression of cellular adhesion molecules and degranulation markers: L-selectin (CD62L) and β_2_-integrin (CD11b) [36]

• Leukocyte apoptotic/necrotic surface and intracellular markers (Annexin V-PE, 7-AAD, Active Caspase-3, Fas (CD95), FasL (CD178) [37-42]

• Soluble pro-/anti-apoptotic molecules (sCD95, sCD95L, TNF-RI, sFas/FasL)[43]

• Leukocyte and endothelial-derived serum soluble adhesion molecule concentrations: intercellular adhesion molecule-1 (sICAM-1), vascular adhesion molecule-1 (sVCAM-1), sE-selectin, sL-selectin [44-46]

• Pro and anti-inflammatory cytokine expression: tumour necrosis factor (TNF)-α, and interleukin (IL)-10 [37,47,48];

• PT/PTT, tissue factor (TF), thrombomodulin (TM), fibrinogen, platelet count and Hg; Ionized calcium, and pH [49]

• Serum sodium, chloride and osmolarity

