### Analysis Plan

This is a feasibility study of two year's duration with a projected screening of 130 patients and recruitment of 100. The primary outcome measure, change in the proportion surviving 30 days post trauma between the treatment and control groups, will be analyzed by means of a generalized linear mixed model which included covariates of interest. The two groups are not expected to be different at baseline, and it is hypothesized that the treatment group would show a 20% decrease in mortality at 30 days post trauma whereas the control group would remain unchanged. To derive a reduced subset of risk factors for the predictor models, acceptable model building strategies are planned (i.e. dropping variables showing extremely small variability and those found to be highly correlated (i.e. correlation coefficient ≥0.8)). Treatment and time factors will be analyzed using a generalized linear mixed models of the secondary outcome repeated measures: the change in mortality after discharge over time as well as the neurocognitive and neuropsychological outcome summary scores. For secondary outcome analyses, the alpha will be adjusted to account for multiple comparisons. Where there is more than one measure for a neuropsychological test (e.g., processing speed, working memory, visuospatial, language, verbal memory, non-verbal memory - with the exception of executive processes, since different measures relate to different brain regions), a composite or prototypical measure will be derived from group comparison. Serial changes in all secondary immune modulation measures, neuro-biomarkers, neurocognitive and neuropsychological outcomes, and structural imaging measures will be evaluated by two-way ANOVA for repeated measures. All analysis will be conducted blinded to treatment assignment.

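### The objective concerns release of neuro-biomarkers, but the plan compares serum concentrations with no allowance for dilution by the randomised fluids

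*Protocol article*

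**What the plan says.** One secondary objective is the effect of HSD on the immuno-inflammatory response and "its effect on modulating the release of neuro-biomarkers into serum" (Study Objective). The word release is attached to the neuro-biomarkers only, which Intervention Protocol lists as S100B, NSE and MBP measured in serum.

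The experimental arm is described as "receiving a single dose 250 ml of 7.5% hypertonic saline in 6% dextran 70". For the other arm, "The study compares a group receiving normal saline according to a paramedic's protocol" (both Study design); no volume is stated in the article.

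On sampling, "Samples of peripheral blood will be collected upon emergency department (ED) arrival, 12, 24 and 48 hours after ED arrival" (Intervention Protocol). No pre-infusion sample is described.

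The laboratory list in Cellular and Molecular Biomarkers includes "PT/PTT, tissue factor (TF), thrombomodulin (TM), fibrinogen, platelet count and Hg", but no role as a dilution reference is given to any of these.

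The Analysis Plan covers "Serial changes in all secondary immune modulation measures, neuro-biomarkers" and the other secondary measures by two-way repeated-measures ANOVA. Covariates are mentioned there only for the 30-day survival model.

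**The concern.** A concentration is an amount divided by a volume, and here the randomised treatment can change the volume. Background presents the experimental fluid in these terms: "Hypertonic Saline provides an alternative to large volume time limited resuscitation to restore hemodynamic stability". A 250 ml dose can stand in for a large volume only if it expands the circulation by more than what is infused. Table 1 (Safety and Dependability) expects sodium up to 158 and osmolarity up to 350 with HSD, which fits a shift of water out of cells.

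With no pre-infusion sample, no marker value is free of the fluid effect. If dilution is greatest at arrival and then fades, it enters both the arm difference and the treatment-by-time term. A difference in S100B, NSE or MBP could then be reported as altered release when only plasma volume differed. The same arithmetic applies to other soluble markers and to cell counts, although their objective is not worded as release.

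**Working it through.** The article gives no figure for dilution, marker spread or marker effect, so there is nothing to reproduce. What follows is an illustration.

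**Inputs from the article:** 250 ml of 7.5% saline in 6% dextran 70; recruitment of 100; packages in blocks of two.

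**Assumed inputs:** body water 42 L, extracellular fluid 14 L, plasma 3.0 L, 290 mOsm/L; 20–25% of any extracellular gain stays in plasma (3.0/14 = 21%); dextran holds either nothing extra or 20–25 ml per gram; 50 patients per arm.

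**Step 1. Plasma gain from HSD**
- Salt load: 75/58.44 × 2 × 1000 × 0.25 = 642 mOsm. Dextran: 60 g/L × 0.25 L = 15 g.
- New osmolality: (42 × 290 + 642)/(42 + 0.25) = 303.5 mOsm/L.
- New extracellular volume: (14 × 290 + 642)/303.5 = 15.49 L, a gain of 1.49 L.
- Plasma gain from salt alone: 0.20 × 1.49 = 0.30 L to 0.25 × 1.49 = 0.37 L.
- With dextran: 0.37 + 0.30 = 0.67 L to 0.37 + 0.375 = 0.75 L.

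**Step 2. HSD/control concentration ratio at equal release**

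Ratio = (3.0 + control plasma gain)/(3.0 + HSD plasma gain). Saline carries 308 mOsm/L, and 25% of its extracellular gain is put in plasma.

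| Control saline | Control plasma gain | HSD gain 0.30 L | 0.37 L | 0.67 L | 0.75 L |
|---|---|---|---|---|---|
| 0.25 L | 0.065 L | 0.93 | 0.91 | 0.83 | 0.82 |
| 1 L | 0.26 L | 0.99 | 0.97 | 0.89 | 0.87 |
| 2 L | 0.52 L | 1.07 | 1.04 | 0.96 | 0.94 |
| 3 L | 0.78 L | 1.15 | 1.12 | 1.03 | 1.01 |

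If both arms receive 1 L of background saline (0.25 L of plasma) and HSD is extra, the ratio is 3.25/(3.25 + HSD gain), or 0.92 to 0.81.

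The ratio crosses 1 between 1 and 2 L of control saline on salt alone, and between 2 and 3 L with dextran. The 1.15 cell takes a 25% plasma share for control saline, 20% for HSD and no dextran effect. With 25% in both arms it is 1.12.

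**Step 3. Chance that dilution alone gives p < 0.05**

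On the log scale with 50 per arm, the chance is about Φ(|ln ratio|/(SD × √(2/50)) − 1.96), where √(2/50) = 0.2.

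| Ratio | log-SD 0.3 | 0.5 | 0.8 | 1.0 |
|---|---|---|---|---|
| 0.90 | 42% | 18% | 10% | 8% |
| 0.85 | 77% | 37% | 17% | 13% |
| 0.82 | 91% | 51% | 24% | 17% |

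These use an unadjusted two-sided 0.05. The Analysis Plan adjusts alpha for secondary outcomes, and fewer than 50 samples per arm are likely, since analysing blood needs consent. Both lower the figures.

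**Step 4. Which correction works**

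Assume 5 L of blood and 3 L of plasma.
- Plasma gain 0.5 L: serum analytes fall to 3/3.5 = 0.857, haemoglobin to 5/5.5 = 0.909. Dividing gives 0.943, so about 6% of dilution remains.
- Plasma gain 0.8 L: 0.789/0.862 = 0.916, so about 8% remains.

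Haemoglobin alone therefore suits cell counts but under-corrects serum analytes. Plasma volume per unit of haemoglobin is (1 − haematocrit)/haemoglobin. At a 0.5 L gain, haematocrit goes from 2/5 = 0.40 to 2/5.5 = 0.364. The factor goes from 0.60 to 0.636/0.909 = 0.70, and 0.70/0.60 = 1.167 = 3.5/3, which cancels the dilution exactly.

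**The case against.** A reader might infer that dilution would make HSD look suppressive, in line with the trial's hypothesis. The documents do not support that. Controls also receive intravenous saline, in a volume not stated here, and the ratio passes through 1 within a plausible range. Dilution within the HSD arm alone (14–21% for an assumed plasma gain of 0.5–0.8 L on 3 L) is not the between-arm bias.

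A reader might also extend the point to every inflammatory marker. The release wording covers only the neuro-biomarkers. Flow-cytometric surface expression is measured per cell and is not changed directly by plasma volume. The panel also includes opposing markers, such as TNF-α and IL-10; a parallel fall in both would not look like a clear anti-inflammatory pattern.

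Nor does any section make the marker results a basis for the definitive trial. Study Objective gives that role to the survival rates.

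Finally, a condensed article may leave assay normalisation to the full protocol, the SAP or a laboratory appendix, so silence about a correction is weak evidence. That stands, and the point does not rest on the silence alone. The article itself sets an objective about release, a measurement of concentration and a named method, and the three do not match. A bias of unknown sign is still enough to prevent reading one as the other.

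**Conclusion.** The mismatch holds: as written, the plan can take a difference in plasma volume for a difference in release. Dilution alone could put the HSD/control ratio anywhere from about 0.81 (small control volume, or equal background fluid) to about 1.15 (about 3 L of control saline), so its direction cannot be stated from the article. At a ratio of 0.85 the chance of a spurious unadjusted p < 0.05 runs from 77% for a tightly distributed marker (log-SD 0.3) to 13% for a widely spread one (log-SD 1.0). The effect is probably largest at arrival; no figure in the article shows whether it persists to 12, 24 or 48 hours.

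All sizes rest on assumed physiology, 50 analysed patients per arm and assumed marker spreads. This concerns secondary measures in a feasibility study. It is worth correcting but does not touch the primary objectives.

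**What to change.** - Keep the raw-concentration analysis in all randomised patients with samples.
- Add a dilution-corrected sensitivity analysis at each draw, using the same-draw blood count. Scale cell counts to haemoglobin, and serum analytes by concentration × (1 − haematocrit)/haemoglobin. Leave per-cell surface markers uncorrected.
- Report total fluid given, by arm.
- Show corrected results with and without post-transfusion samples. Only excluding them would select on a post-randomisation event that may differ by arm.
- Claim an effect on release only if raw and corrected results agree. Otherwise word the conclusion as an effect on serum concentration.

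The cost is some extra analysis, using a value that appears to be collected already. This assumes that Hg means haemoglobin and that the same blood count supplies haematocrit, which the article does not list. Without a pre-infusion draw, the corrected value is an amount per unit of circulating haemoglobin. It therefore also moves with bleeding and transfusion and is noisier than the raw value, so it should remain a sensitivity analysis.

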### Randomization

The study employs a block randomization by station derived from a computer-generated random number table. Blocks of two study packages are assigned to each ambulance vehicle/aircraft. Paramedics are blinded to the treatment assigned until package opening. A field logistics research coordinator is responsible for randomization compliance at the vehicle level through daily checks. Compliance at the patient will be verified through the randomization number of the product label and recorded on the data checklist.

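### If each vehicle's pair of packages holds one of each arm, the second allocation is predictable to a crew that knows the first, and selective enrolment can bias the comparison of arms

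*Protocol article*

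**What the plan says.** All the relevant text is in the Randomization section of the protocol article. It first gives the station as the unit: "The study employs a block randomization by station derived from a computer-generated random number table". It then gives the block size and where the block is held: "Blocks of two study packages are assigned to each ambulance vehicle/aircraft". Concealment is claimed up to a stated moment: "Paramedics are blinded to the treatment assigned until package opening".

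Two checks are named. At vehicle level, "A field logistics research coordinator is responsible for randomization compliance at the vehicle level through daily checks". At patient level, compliance is "verified through the randomization number of the product label and recorded on the data checklist".

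The Study design section describes two arms: "The study compares a group receiving normal saline according to a paramedic's protocol, with a treatment group receiving a single dose 250 ml" of HSD. The Analysis Plan gives a "projected screening of 130 patients and recruitment of 100", and hypothesises that "the treatment group would show a 20% decrease in mortality at 30 days post trauma". The Study Objective section makes survival by arm and the randomization compliance rate two of the four primary feasibility endpoints. Ethical Considerations describes a waiver of consent.

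**The concern.** A block of two across two arms is balanced only if it holds one package of each. When the first is opened its arm is seen, and the package left on that vehicle must be the other arm. The people who open packages also decide in the field, without a consent step, whether to enrol.

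A crew that knows the next arm can let that knowledge affect whether a given patient is entered. The Discussion section shows how widely prognosis varies among patients who meet the Glasgow Coma Scale criterion: some die in the Emergency Department, while others turn out to be affected by alcohol or drugs and go home within hours. If crews can partly tell these apart, even modest selection shifts survival by arm. The Analysis Plan expects the arms to be alike at baseline, which depends on concealment. The survival rates by arm are meant to feed the design of a definitive multicentre trial, so a distortion would be carried forward, and so might the allocation procedure.

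**Working it through.** The article states no figure for predictability, so there is none to reproduce.

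**Inputs.** From the article: block size 2, held on one vehicle or aircraft; arm seen at opening; two arms; 100 patients. Inferred: one package per arm in each pair. Assumed, because not stated: the number of vehicles, the behaviour of crews and mortality.

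**1. Predictability within a block.** For a balanced block of size 2b whose size is known, the share of allocations fully determined by earlier ones is 1/(b+1). The best-guess success rate is [b + (4^b/C(2b,b) − 1)/2]/(2b).

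| Block size | Determined | Best guess correct |
|---|---|---|
| 2 | 1/2 = 50% | [1 + (4/2 − 1)/2]/2 = 75% |
| 4 | 1/3 = 33.3% | [2 + (16/6 − 1)/2]/4 = 70.8% |
| 6 | 1/4 = 25% | [3 + (64/20 − 1)/2]/6 = 68.3% |

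Simple randomisation gives 50% correct guesses. Enumerating all balanced blocks gives the same values.

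**2. How many patients are second in a pair.** Suppose 100 patients fall at random on V equally busy vehicles and a pair stays on board until both packages are used. The number of completed pairs on a vehicle is half its patient count, rounded down, so the expected total is 50 − (V/4)[1 − (1 − 2/V)^100].

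- V = 5: 50 − 1.25 × 1.00 = 48.75, about 49
- V = 20: 50 − 5 × 1.00 = 45
- V = 40: 50 − 10 × 0.994 = 40
- V = 100: 50 − 25 × 0.867 = 28
- V = 200: 50 − 50 × 0.634 = 18

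A simulation agrees to within 0.1 patient. Fifty is the ceiling, reached only if every pair is completed.

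**3. Possible bias.** Let f be the share of patients in predictable slots. Assume crews act on the knowledge in 30% of those slots, and that the patients so steered to the two arms differ by 20 points in mortality. The bias is f × 0.30 × 20:

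- f = 0.18: 1.1 points
- f = 0.28: 1.7 points
- f = 0.49: 2.9 points

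A second illustration assumes no treatment effect, half the patients at 15% mortality and half at 55%. Crews skip a share q of low-risk patients when HSD is next, and the same share of high-risk patients when saline is next. In predictable slots, q = 0.25 makes 57.1% of HSD patients high-risk against 42.9% of saline patients, a gap of 0.40 × 14.3 = 5.7 points. With q = 0.5 the shares are 66.7% and 33.3%, a gap of 13.3 points. Multiplying by f gives 1.1 to 2.7 points at f = 0.2 and 2.9 to 6.7 points at f = 0.5. The size rests entirely on these assumptions.

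**4. What the checks can see.** The label number shows which package a patient received, and the daily check covers compliance at the vehicle. Neither would show that an eligible patient was passed over. Blinded outcome review (Safety and Dependability) and blinded analysis (Analysis Plan) act after enrolment.

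**The case against.** The case against is substantial, and much of it limits the point.

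- **The one-plus-one pair is inferred.** The section names both the station and the vehicle. If the list is blocked at station level and two packages are only the vehicle's stock, the second is not determined. This stands as a condition, although the article itself calls the pair a block.
- **Certainty for every pair.** A reader might infer that the crew always knows the second arm. That requires the crew facing the second package to know what the first contained. The Setting section lists about 430 advanced life support paramedics and 32 flight paramedics for 100 patients over two years, so a repeat by the same crew may be uncommon. A coordinator also checks vehicles daily. Whether a half-used pair is swapped is detail that an article may leave to the full protocol, so its absence here is not a fault.
- **Size.** A reader might take 50 of 100 as the expected number, or set 3 points of bias against a target of 5 to 10 points. The first is a ceiling. The second assumes that the 20% is relative and that control mortality is 25% to 50%; neither is stated, and an absolute reading makes the target 20 points. Crews with mixed preferences would partly cancel out. With 50 per arm at those mortalities, the 95% half-width of the difference is 1.96 × √(2p(1 − p)/50), or about 17 to 20 points.
- **Compliance.** A reader might infer that the compliance endpoint is itself corrupted. It is measured by package label, and skipping a patient leaves it unchanged.
- **Context.** This is a feasibility study, eligibility uses a coma-scale criterion, and the survival model includes covariates. These limit the harm but do not restore concealment.

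**Conclusion.** The point holds conditionally. On the natural reading of the Randomization section, a pair held on one vehicle and unblinded at opening makes the second allocation predictable to any crew that knows the first. Selective enrolment can then bias all between-arm comparisons, including survival by arm. Half of the allocations in completed pairs are determined. About 18 to 49 of 100 patients would be second in a pair for an assumed 200 down to 5 vehicles, with fewer actually predictable after crew turnover.

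The bias, about 1 to 3 points under the 30% steering and 20-point assumptions, is a possibility and has not been shown. The compliance rate is not distorted, but it is uninformative here: it could look perfect although concealment had failed. The documents support a cheap improvement to a stated design rule. They do not support a claim that the trial's results are biased.

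**What to change.** Name one unit of blocking, the station or air base, and remove the conflict with the vehicle. Generate the list at that level with randomly varying, undisclosed block sizes, for example 4 and 6, so that the packages on a vehicle do not form a complete block. Have the field logistics coordinator, who already makes daily checks, replace each used package singly with the next number on the list. Record the order of opening so that use can be checked against the list.

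If two packages on a vehicle come from the same block of size 2b, the one remaining is of the opposite arm with probability b/(2b − 1). That is 2/3 for a block of 4 and 3/5 for a block of 6, against 1 for a block of 2. Predictability is reduced, not removed.

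The cost is a new list and a restocking rule before enrolment. Arm balance becomes somewhat looser within vehicles, and possibly overall if station-level blocks stay incomplete with only 100 patients. The coordinator's added workload cannot be sized without station and vehicle numbers.
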